## Abstract

**Background:**

Recent randomized controlled trials (RCTs) in patients with prolonged disorders of consciousness (pDoC) have yielded limited success. Among them, only studies involving amantadine have provided Class II evidence. The effects of other non-invasive brain stimulation techniques remain inconclusive, largely due to patient heterogeneity and the clinical complexities of implementing such interventions. Low-intensity focused ultrasound pulses (LIFUP), as a novel, non-invasive, and safe neuromodulation technique, have the potential to both stimulate and inhibit deep subcortical structures. This makes LIFUP a promising approach for modulating consciousness and promoting recovery in patients with pDoC. This study aims to evaluate the therapeutic efficacy and safety of LIFUP through a randomized controlled design.

**Methods and analysis:**

Our primary research focus involves conducting multimodal neurofunctional assessments throughout the intervention period. Specifically, we intend to investigate the relationship between Blood Oxygen Level-Dependent (BOLD) signals, electroencephalography (EEG) patterns, thalamic concentrations of glutamate and glutamine (Glx) and gamma-aminobutyric acid (GABA) and behavioral outcomes under two different LIFUP parameter settings (100 Hz transcranial ultrasound stimulation [TUS] and theta-burst TUS [tbTUS]).

**Discussion:**

Through a comprehensive exploration of parameter setting combined with multimodal neurofunctional assessments, this study evaluates both therapeutic potential and safety considerations of ultrasound-based interventions for pDoC. We hypothesize that the two stimulation protocols (100 Hz TUS and tb TUS) will differentially modulate neural connectivity, thalamus activity, and the Glx/GABA balance. The findings may advance evidence-based interventions for pDoC and identify potential neuroplasticity biomarkers to guide future therapeutic strategies.

**Clinical trial registration:**

Chinese Clinical Trial Registry, ChiCTR2400092904. Registered on 26 November 2024.

## Introduction

1

Consciousness is a fundamental aspect of human existence and has long intrigued both philosophers and scientists alike (1). In a clinical context, Plum and Posner proposed that consciousness can be conceptualized as comprising two principal dimensions: arousal, referring to wakefulness, and awareness, referring to subjective experience or phenomenology (2). However, evaluating the presence of consciousness in individuals who have survived severe brain injury remains a significant challenge. Clinically, the assessment of consciousness and its disorders primarily depends on observable behavior to infer the patient’s level of consciousness (3). Disorders of consciousness (DoC) encompass conditions marked by altered arousal and awareness (4), including coma (a state of complete unresponsiveness without wakefulness) (2), vegetative state (VS) (5), also referred to as Unresponsive Wakefulness Syndrome (UWS) (6) and the minimally conscious state (MCS) (7). The VS is a state of wakefulness without awareness in which there is preserved capacity for spontaneous or stimulus-induced arousal evidenced by sleep–wake cycles and a range of reflexive and spontaneous behaviors (5). In contrast, MCS patients show intermittent signs of awareness and may slowly regain some cognitive function (7). Among patients with prolonged disorders of consciousness (pDoC)(any disorder of consciousness that has continued for at least 4 weeks following sudden onset brain injury) (5), predicting recovery remains fraught with uncertainty. Nevertheless, both in the acute and chronic stages of DoC, there were documented cases of patients gradually regaining consciousness and functional abilities over time^4.5^. This capacity for recovery has drawn significant interest in the neuroscience community (4). Some studies suggested that the nervous system may retain viable neurons even during severe stress states, and that not all neural populations were uniformly affected by the initial insult (8, 9). The body may activate intrinsic protective mechanisms, as observed in patients who regain consciousness after cardiac arrest or COVID-19-related coma (8). A notable study of 50 patients with chronic VS/UWS (duration >6 months) followed for nearly 2 years found that 6 patients (12% of the sample) ultimately recovered consciousness (10). These findings underscored the clinical significance of pursuing effective interventions and treatments aimed at enhancing the potential for recovery in patients with pDoC (11).

Currently, despite a growing landscape of studies investigating non-invasive neuromodulatory treatments for pDoC (12, 13), none has yet been established to systematically improve consciousness levels or functional recovery in this population. First, regarding transcranial direct current stimulation (tDCS) (14), a multicenter randomized clinical trial conducted in 2023 evaluated the effects of tDCS during rehabilitation. While no significant therapeutic effect was observed at the group level, subgroup analysis at a 3-month follow-up revealed notable improvements in patients with minimally conscious state (MCS) and traumatic etiologies. Second, in the field of transcranial magnetic stimulation (TMS) (15), repetitive TMS (rTMS) applied to the dorsolateral prefrontal cortex in 16 patients with DoC (5 MCS and 11 VS/UWS) resulted in increased (the Coma Recovery Scale-Revised) CRS-R scores in 36% of VS/UWS patients and all MCS patients. Moreover, a 2022 study applying 20 Hz rTMS (16) demonstrated significant improvements in consciousness in the real stimulation group compared to the sham group. However, in-depth analysis revealed that only a subset of patients experienced clinically meaningful gains. Third, for transcutaneous auricular vagus nerve stimulation (taVNS), a 2023 randomized double-blind controlled trial (17) involving 57 DoC patients found that while the intervention group showed higher CRS-R scores post-treatment compared to the control group, the difference did not reach statistical significance. Finally, in the realm of Low-intensity focused ultrasound pulses (LIFUP), Monti et al. (18) pioneered the use of non-invasive ultrasound to stimulate the thalamus (100 Hz TUS) in a patient with MCS following traumatic brain injury in 2016. The patient exhibited significant clinical improvement, marking a pivotal moment in the application of LIFUP for DoC. Subsequent studies have reported increases in CRS-R scores in both acute (19) and chronic (20) DoC cases. However, The absence of rigorous comparison with a sham stimulation group limits these findings, highlighting the need for controlled investigations.

LIFUP holds substantial promise as a noninvasive modality for modulating human neural circuits (21). Compared to conventional non-invasive brain stimulation techniques, ultrasound offers unparalleled spatial precision, capable of targeting both cortical and deep subcortical brain structures with a resolution on the order of just a few cubic millimeters. This high degree of focus allows for the precise stimulation of small subcortical regions, such as the thalamus, which previously required invasive deep brain stimulation (DBS) techniques (21). Moreover, LIFUP is regarded as a highly safe method of neuromodulation (22, 23). Given the heterogeneity among patients with DoC, LIFUP presents a promising therapeutic avenue, though its clinical efficacy remains to be confirmed through well-designed randomized controlled trials. The underlying mechanisms of LIFUP are not yet fully elucidated. A prevailing hypothesis suggests that the acoustic pressure delivered by LIFUP induces nanoscale deformation of neuronal membranes, which may modulate the activity of ion channels and mechanosensitive receptors embedded in the membrane (22, 23). In particular, LIFUP may alter the function of mechanosensitive ion channels, influencing the excitability and spontaneous firing rates of neurons, thereby inducing both short-term and long-term neuroplastic changes (21–23). These physiological effects may further result in modulations of cerebral blood flow, the release and uptake of neurotransmitters, and ultimately, alterations in neural circuit function (24–26). As such, LIFUP represents a compelling tool for investigating and potentially restoring consciousness in patients with DoC.

In 2021, Cain et al. (20) conducted a pilot intervention using thalamic LIFUP on three patients with pDoC, of whom two demonstrated significant improvements in behavioral responsiveness compared to baseline. In 2022, a similar intervention (19) was applied to 11 patients with acute DoC, with nine exhibiting behavioral improvements. Both studies reported favorable safety profiles and a high response rate. However, these proof-of-concept case series lacked a sham-controlled condition, limiting the strength of causal inferences. In a separate 2022 study (27), an 80-s train of theta-burst patterned transcranial ultrasound (tbTUS) was applied to the motor cortex of 15 healthy participants. The results revealed elevated corticospinal excitability sustained for up to 30 min, alongside reduced short-interval intracortical inhibition and enhanced intracortical facilitation, suggesting that tbTUS may promote long-term cortical plasticity. Given the operational characteristics of LIFUP, thalamic stimulation using specific parameter sets may likewise elicit excitatory effects and induce plastic changes within thalamic circuits. However, no studies to date have directly compared the effects of different LIFUP parameter configurations, specifically, 100 Hz TUS and tbTUS in patients with pDoC. This represents a critical gap in current knowledge. Investigating whether these parameters produce differential outcomes and how they modulate neural functional connectivity, neurotransmitter dynamics, and EEG signal features is essential. Such insights could optimize treatment protocols and advance our understanding of the neurobiological mechanisms underlying recovery in pDoC.

Based on the above, this study aims to evaluate the efficacy and safety of LIFUP as a potential neuromodulatory treatment. Another major focus of our investigation is to explore the relationship between multimodal neurofunctional assessments and behavioral outcomes in patients with pDoC. We hypothesize that participants receiving LIFUP delivered via either 100 Hz TUS or tbTUS will exhibit significantly improved behavioral recovery metrics compared to sham-controlled participants. Furthermore, we predict that 100 Hz TUS (19, 20) will induce superior neuroplastic effects relative to tbTUS (27), as quantified through multimodal functional connectivity analyses. These differential effects are anticipated to manifest as: (1) increased phase-locking value (PLV) in whole-scalp or region-specific high-density electroencephalography (HD-EEG), and (2) enhanced effective connectivity (EC) in task-based functional magnetic resonance imaging (fMRI), particularly within targeted neuromodulation networks.

## Methods and analysis

2

### Study design

2.1

This is a single-site, controlled randomized trial conducted at the Intensive Care Rehabilitation Ward of Shanghai Yangzhi Rehabilitation Hospital, also known as the Shanghai Sunshine Rehabilitation Center. In this parallel-group study, 78 patients with pDoC will be prospectively randomized in a 1:1:1 ratio to one of three arms: Group A (100 Hz TUS), Group B (tbTUS), or Group C (sham LIFUP stimulation).

All enrolled patients will receive two sessions of TUS treatment whether it is real or sham stimulation. In addition to CRS-R assessments, comprehensive neurophysiological and neuroimaging assessments, including HD-EEG, Somatosensory Evoked Potentials (SSEPs), fMRI, proton magnetic resonance spectroscopy (MRS) and positron emission tomography-computed tomography (PET-CT), will be performed at baseline (pre-treatment) and follow-up (post-treatment) time points. Longitudinal outcome measures will be assessed at three timepoints: 1 month (30 ± 7 days), 3 months (90 ± 14 days), and 6 months (180 ± 30 days) following the final intervention.

During each treatment session, vital signs including body temperature, heart rate, blood pressure, and respiratory rate will be monitored to ensure safety. The vital signs of the patients will be continuously monitored 24 h after the intervention. The trial will be supervised by a team comprising at least one neurologist, one neurorehabilitation specialist, and associated research staff. All procedures and evaluations will adhere strictly to the study protocol. A schematic flow chart of the trial design is provided in Figure 1.

**Figure 1 fig1:**
[figure not shown]
Flow diagram of the study.

### Selection of subjects

2.2

#### Inclusion criteria

2.2.1

Participants must have sustained their injury or onset more than 28 days prior to enrollment;Participants must be over 18 years of age;Participants must exhibit a behavioral profile consistent with either a VS/UWS or a MCS, as assessed by the CRS -R;Participants must not have experienced any significant fluctuations in their medical condition during the past week. Common causes of instability include fever exceeding 37.3 °C within the past 7 days, epileptic seizures, paroxysmal sympathetic hyperactivity, and inability to maintain adequate oxygenation for 40 min. The above conditions will be assessed by two ICU physicians based on the patient’s status over the recent week.

#### Exclusion criteria

2.2.2

Participants with significant/severe cardiac disease;Participants with a history of neurological illness prior to the current injury;Participants who are unable to safely undergo MRI scanning due to a severe infection;Participants with intracranial metal implants.

All patients will be recruited from the intensive care and rehabilitation wards. The study will be conducted from March 2025 to December 2025. Potential participants will be identified by reviewing electronic medical records within the hospital information system (HIS). Researchers will explain the details of the study to the patients’ legal guardians. Upon obtaining consent, a neurologist will evaluate each candidate based on the inclusion and exclusion criteria. Those who meet the eligibility requirements will be formally invited to participate in the study and will undergo a comprehensive neurological examination, followed by a rehabilitation assessment, prior to the intervention.

#### Sample size

2.2.3

For the behavioral assessment using the CRS-R, this study adopts a randomized controlled intervention design. Repeated measures will be analyzed using ANOVA to account for potential confounding variables. Based on a power analysis conducted using G*Power, with an effect size of 0.40, a significance level (*α*) of 0.05, statistical power (1 − *β*) of 0.80, a two-tailed test (α = 0.05), and an equal allocation ratio among the three groups (N1: N2: N3 = 1:1:1), the required each group sample size is calculated to be 18. After applying Bonferroni correction, the significance threshold for individual comparisons should be adjusted to α = 0.0167. To maintain this corrected alpha level, each group would require a sample size of 22. Considering a potential 15% dropout or exclusion rate, a minimum of 76 participants is required. Therefore, the study will enroll a total of 78 participants: 26 in Group A, 26 in Group B, and 26 in Group C. In the event of patient withdrawal or death during the study, we will implement standardized procedures. All withdrawal cases will be documented systematically, including: (1) voluntary withdrawal (participant-initiated consent revocation), (2) loss to follow-up (≥3 consecutive contact attempts failed), (3) clinical deterioration (≥2-point GCS decrease sustained for 48 h), and (4) investigator-determined withdrawal (with protocol-specified justification). For data management, all collected pre-withdrawal data will be retained per intention-to-treat principles, with final evaluable assessments carried forward for primary analysis. Mortality cases will trigger immediate reporting to the Ethics Committee of Shanghai Yangzhi Rehabilitation Hospital (Shanghai Sunshine Rehabilitation Center), followed by survival analysis using Kaplan–Meier methodology and independent adjudication of causes by a clinical endpoint committee. Statistical approaches will include sensitivity analyses (completers vs. non-completers) and multiple imputation for missing data.

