### Outcome measures

2.4

The primary outcome of this study is the recovery of consciousness measured by CRS-R and CRS-R_index_. Secondary outcomes will include the assessment of neurophysiological changes through multimodal neuroimaging and electrophysiological measures (fMRI, MRS, EEG) to evaluate intervention efficacy and safety. Additionally, SSEPs and PCT-CT measurements will be obtained at both baseline and endpoint assessments. These measurements will provide valuable insights into the impact of the study and aid in further understanding the research findings. Any adverse outcomes or side effects will be documented throughout the treatment process.

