### Data analysis

2.5

We will perform a comprehensive analysis combining behavioral outcomes of CRS-R_index_ (R code available at)^2^ and neuroimaging data (fMRI, MRS, PET-CT). Statistical analyses will be conducted at both the individual and group levels, comparing outcomes before and after treatment, as well as between intervention and control groups. The main statistical approach will include repeated-measures ANOVA to examine within- and between-group effects, accounting for potential confounding variables. Continuous variables will be analyzed using paired or independent sample t-tests, while categorical variables will be assessed using the Mann–Whitney U test. Chi-square tests or Fisher’s exact tests will be employed to evaluate and document adverse events. To explore associations between neurotransmitter concentrations and other outcomes, regression analyses will be conducted. For SSEPs, changes in amplitude and latency before and after treatment will be compared using t-tests. EEG data will be analyzed using EEGLAB (41) to evaluate both local and cross-regional functional connectivity metrics, including phase locking value (PLV) and power spectral density (PSD). Functional MRI assessments will be conducted using SPM12 (36) to examine seed-to-seed functional and effective connectivity during both resting-state and task-based conditions. MRS will be primarily employed to compare pre- and post-treatment changes in Glx and GABA concentrations within the stimulated brain regions. Additionally, PET-CT imaging will be used to assess alterations in glucose metabolism, both in the stimulated areas and across the whole brain, following the intervention. For fMRI or EEG data analysis, we will implement FDR or FWER correction for multiple comparisons, but will not utilize machine learning validation approaches.

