The mechanism underlying recovery from pDoC remains poorly understood. At the level of neural functional connectivity, pDoC was associated with severe disruptions in resting-state network connectivity, particularly within higher-order networks (46). Interestingly, has been observed in the limbic system including the orbitofrontal cortex, insula, hypothalamus, and ventral tegmental area in patients with VS/UWS (47). Such hyperconnectivity may reflect early-stage injury responses, as brain injury often disrupted normal neural connectivity and may initially provoked compensatory overactivation (48). As described in studies of DBS, stimulation of the central thalamus could both increase and decrease functional connectivity, suggesting that the brain may adjust connectivity toward a balanced, homeostatic state during recovery (49). While tbTUS demonstrate excitatory (27) cortical effects, its deep nuclear actions appear more complex. Notably, recordings of local field potentials in the internal globus pallidus during intervention of 120 s tbTUS in DBS-implanted patients revealed enhanced theta and beta activity, though the underlying excitatory/inhibitory mechanisms remain to be elucidated (50). This temporal and spatial complexity suggests ultrasound’s therapeutic effects may vary by both disease stage and anatomical target. Finally, we suggest that the mechanisms underlying the recovery of DoC require more precise experimental designs of TUS. In the future, this approach could potentially be combined with DBS-implanted patients.

To our knowledge, this is the first randomized controlled trial to investigate the effects and safety of LIFUP on patients with pDoC. We aim to compare the effects of two different parameter sets (100 Hz TUS and tbTUS), and to explore the relationship between behavioral recovery in pDoC and BOLD and EEG signal changes, as well as thalamic concentrations of Glx/GABA. These findings may contribute to a better understanding of the neurobiological mechanisms underlying recovery in pDoC.

However, it should be noted that this is a single-center clinical trial. Future multicenter studies with larger sample sizes will be necessary to validate these results. Moreover, whether the optimal stimulation target should be the left thalamus or bilateral thalami remains an open question, requiring further clinical investigation.

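### Single-step Bonferroni over three CRS-R comparisons is valid but needlessly conservative: a closed or step-down rule would gain about 9 to 12 points of power per active-sham contrast at 22 per arm, with no extra patients

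*Protocol article*

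**What the plan says.** Section 2.2.3 (Sample size) sizes the trial on the CRS-R with three equal arms, an effect size of 0.40, α = 0.05 two-tailed and power 0.80, and obtains 18 per group. It continues: "After applying Bonferroni correction, the significance threshold for individual comparisons should be adjusted to α = 0.0167". The group size then rises to 22, and 26 per arm are enrolled. The value 0.0167 is 0.05/3, so three pairwise comparisons are implied, though not listed.

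The Introduction states the behavioural hypothesis as two contrasts: "participants receiving LIFUP delivered via either 100 Hz TUS or tbTUS will exhibit significantly improved behavioral recovery metrics compared to sham-controlled participants". Its prediction about one active setting against the other rests on a different kind of measure: "we predict that 100 Hz TUS (19, 20) will induce superior neuroplastic effects relative to tbTUS (27), as quantified through multimodal functional connectivity analyses". The Discussion states a more general aim, without an endpoint: "We aim to compare the effects of two different parameter sets (100 Hz TUS and tbTUS".

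Section 2.4 makes the CRS-R and its index the primary outcome. Section 2.5 (Data analysis) says: "The main statistical approach will include repeated-measures ANOVA to examine within- and between-group effects".

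**The concern.** The multiplicity rule does not follow the behavioural hypothesis. Two CRS-R contrasts carry that hypothesis, yet α is divided by three. The correction is also applied in one step, the least powerful of the common ways to protect a family of three pairs.

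In a single-centre trial of 78 patients, what is at stake is the chance of detecting a real benefit of either setting over sham. The error rate is not at stake.

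**Working it through.** **Inputs.** From section 2.2.3: effect size 0.40, α = 0.05 two-tailed, three equal arms, 22 per arm after correction, 26 enrolled. Assumptions, since the article does not state them: 0.40 is Cohen's f, and both active arms are equally effective, in line with the behavioural hypothesis.

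**1. The plan's own figures.**
- 0.05/3 = 0.0167, as stated. The two active-sham contrasts together hold 2 × 0.0167 = 0.0333, and the active-active contrast holds the remaining 0.0167.
- For the between-group F test in a repeated-measures ANOVA, the noncentrality is f² × 3n × m / (1 + (m − 1)ρ). With assumed m = 2 measurements and ρ = 0.5 this is 0.16 × 3n × 2 / 1.5 = 0.64n. Power 0.80 then needs 17 per group at 0.05 (stated 18) and 22 at 0.0167 (stated 22).
- A one-way ANOVA at one time point needs 22 and 28, so it does not reproduce the plan. The article gives neither m nor ρ, so both models are carried below.

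**2. From f to a pairwise difference.** With arm means d, d and 0, the standard deviation of the means is d√2/3. Setting this to 0.40 gives d = 1.2/√2 = 0.849 at a single time point. Averaging two measurements with ρ = 0.5 multiplies the SD by √(1.5/2) = 0.866, so d = 0.849/0.866 = 0.98.

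**3. Rules compared.** All use the pooled variance on 3 × 22 − 3 = 63 degrees of freedom and noncentrality d√(n/2) per pair. The stepwise and gated rules were simulated.

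| Rule | Power per active-sham contrast, d = 0.849, n = 22 | d = 0.98, n = 22 |
|---|---|---|
| Bonferroni over three (plan) | 64% | 78% |
| Bonferroni over two | 70% | 83% |
| Closed: omnibus F at 0.05, then each of three pairs at 0.05 | 74% | about 87% |
| Holm on two contrasts | 75% | about 87% |
| Step-down Dunnett on two contrasts | 76% | about 87% |

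At d = 0.849, the power to show that both arms beat sham is 49% under the plan's rule and 66% to 67% under the last three.

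**4. Error rate.** Family-wise error under the complete null is about 4.4% for the plan's rule, 4.6% for Holm, and 5.0% for step-down Dunnett and the closed test. The closed test needs no further adjustment with exactly three arms. Any two of the three pairwise nulls imply that all three means are equal, so the omnibus F already tests every intersection.

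**5. Sensitivity.**
- If only the 100 Hz arm works (0.849 SD, n = 22), its power is 64% under the plan's rule, 70% with Holm, 71% with step-down Dunnett and about 74% with the closed test.
- If all 26 per arm are evaluable and both arms work at d = 0.849, it is 73% under the plan's rule and 82% to 83% under the alternatives.
- At d = 0.98 with 26 per arm, the plan's rule gives 86%. An unadjusted test at 0.05 gives 94%, so no alternative can gain more than 94 − 86 = 8 points.

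**The case against.** Bonferroni at 0.05/3 is a valid choice, and the plan raises its group size from 18 to 22 to pay for it. Comparing the two settings is a declared aim: the Introduction calls the missing comparison a gap, and the Discussion repeats the aim. Both points stand.

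Three stronger readings are tempting, and the documents do not support them.

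- *A third of α is wasted, at a cost of about 10 points.* Dividing by three rather than two costs about 6 points at a single time point (64% against 70%) and about 5 under the repeated-measures model (78% against 83%). The rest of the gain comes from replacing a single-step rule by a stepwise or closed one. The closed test shows this, since it keeps all three pairs and still gains 10 points at d = 0.849. Because the active-active comparison is a stated aim, reserving α for it is defensible.
- *The trial could reach opposite conclusions because its deciding test is open.* Section 2.5 does speak loosely of "comparing outcomes before and after treatment, as well as between intervention and control groups", which might suggest pooling the active arms. Section 2.2.3, however, refers to individual comparisons among three groups, which points to pairwise tests. A significant omnibus F without a significant active-sham pair is no contradiction, because the F also reflects the active-active difference. The exact list of contrasts is commonly left to an analysis plan that is not shown here.
- *Power is only 64%.* That figure belongs to the single-time-point model, which does not reproduce the plan's group sizes. Under the model that comes close, it is 78%.

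**Conclusion.** The point holds as one of efficiency. The stated rule controls the family-wise error but is needlessly conservative for a behavioural hypothesis made of two active-sham contrasts. With both arms effective and 22 per arm, a closed or step-down rule gains 10 to 12 points per contrast at a single time point, and about 9 under the repeated-measures model. If all 26 per arm are evaluable, the gains are about 9 to 10 points and at most 8 points respectively.

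The figures rest on reading 0.40 as Cohen's f and on the assumed m = 2 and ρ = 0.5. They also assume one CRS-R measure tested once, whereas section 2.4 names both the CRS-R and its index.

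**What to change.** Amend sections 2.2.3 and 2.5 in one of two ways.

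1. **Keep all three CRS-R pairs confirmatory.** Replace single-step Bonferroni by the closed procedure for three arms: the between-group omnibus test at 0.05 on one pre-named CRS-R measure and, only if it is significant, each pair at two-sided 0.05.
2. **Make the active-active CRS-R comparison secondary.** Test 100 Hz TUS against sham and tbTUS against sham by Holm or step-down Dunnett at two-sided family-wise 0.05.

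Either way the cost is a few sentences, with no change in enrolment or data collection. The simple simultaneous confidence intervals that Bonferroni supplies are lost. Under the second option the active-active CRS-R comparison is also no longer confirmatory. The prediction of a difference between the two settings on connectivity measures is unaffected.

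### The primary analysis carries the last assessment forward for withdrawn patients, including those withdrawn because they deteriorated; the scope of the rule for deaths and the role of multiple imputation are left unclear

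*Protocol article*

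**What the plan says.** The rules stand in the protocol article, section 2.2.3 (Sample size). They open with both events together: "In the event of patient withdrawal or death during the study, we will implement standardized procedures". Four withdrawal reasons follow: revoked consent, loss to follow-up, deterioration defined as "clinical deterioration (≥2-point GCS decrease sustained for 48 h"), and the investigator's decision. Data collected before withdrawal are kept on intention-to-treat grounds, "with final evaluable assessments carried forward for primary analysis". No withdrawal reason is exempted.

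Deaths have their own sentence: reporting to the ethics committee, "followed by survival analysis using Kaplan–Meier methodology and independent adjudication of causes by a clinical endpoint committee". It assigns no CRS-R value. The paragraph ends: "Statistical approaches will include sensitivity analyses (completers vs. non-completers) and multiple imputation for missing data".

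On the endpoint, section 2.4 states: "The primary outcome of this study is the recovery of consciousness measured by CRS-R", together with the CRS-R index. Section 2.4.1 uses the index for the group comparison and averages the scores of the two sessions. Section 2.3 places CRS-R one hour before and after each session, with the sessions 2 to 3 days apart. Sections 2.1 and 2.3.6 add CRS-R at 1, 3 and 6 months. Section 2.5 names repeated-measures ANOVA as the main approach.

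**The concern.** Carry-forward assumes that a patient's score would not have changed after the last assessment. That assumption is least credible for a patient withdrawn for a sustained fall in GCS, since responsiveness is close to what the CRS-R measures. The missingness is then informative by the protocol's own definition, and the value filled in may come from before the fall. If one arm has more such withdrawals, part of its disadvantage drops out of the efficacy comparison.

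The error can also run the other way. A patient lost early for an unrelated reason is held at an early score while others may go on recovering, which penalises the arm with more early loss. In both cases the ANOVA treats filled-in values as measured ones, so standard errors tend to be too small.

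Two ambiguities add to this. A reader cannot tell whether a death carries its last CRS-R forward, or whether multiple imputation is the primary method, a sensitivity analysis or a method for other variables.

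**Working it through.** **How many patients.** The plan needs 22 per group, or 66 in all, and allows 15% dropout. 66 × 1.15 = 75.9, which gives the stated minimum of 76; 66 / 0.85 = 77.6, which gives the 78 enrolled. So 0.15 × 78 = 11.7, about 12 patients, or 0.15 × 26 = 3.9, about 4 per arm, could have a carried-forward value if the planned dropout occurs.

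**Formula.** In one arm let *p* be the share withdrawn and *d* their mean change after the last assessment. Carry-forward sets *d* to 0, so the arm mean is off by −*p* × *d*. The difference between arms A and C is off by −(*p*A × *d*A − *p*C × *d*C). If the later change is a worsening of *w* in both arms (*d* = −*w*), this becomes (*p*A − *p*C) × *w*, in favour of the arm with more withdrawals.

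**Numbers.** The protocol gives neither dropout by arm nor the size of the worsening, so both are assumptions. Take *p* = 0.20 in one arm and 0.10 in the other, a difference of 0.10 × 26 = 2.6 patients:

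| Unobserved worsening *w* | Bias in the arm difference |
|---|---|
| 0.5 SD | 0.10 × 0.5 = 0.05 SD |
| 1 SD | 0.10 × 1 = 0.10 SD |
| 2 SD | 0.10 × 2 = 0.20 SD |

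Swapping the two shares reverses the sign. If withdrawn patients would have improved instead, the bias has the same size but goes against the arm with more withdrawals. With 15% in both arms and the same *w*, the between-arm bias is 0, but each arm mean is overstated by 0.15 × *w* (0.075 to 0.30 SD).

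**Scale.** Suppose the planned effect size of 0.40 is Cohen's f and the two active arms are equal, each differing from sham by D standard deviations. The variance of the three means is 2D²/9, so f = D × √2 / 3 and D = 0.40 × 3 / 1.414 = 0.85 SD. A bias of 0.05 to 0.20 SD is then about 6% to 24% of the planned difference (0.05 / 0.85 and 0.20 / 0.85).

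**Dependence on the time point.** On section 2.4.1's wording the group analysis uses scores around two sessions 2 to 3 days apart. Carry-forward then bridges days, *d* is small, and few patients can be affected. If the 1, 3 and 6 month scores of sections 2.1 and 2.3.6 enter the ANOVA, carry-forward can bridge up to about 6 months, and both *p* and *d* grow. The article does not settle which reading applies.

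**The case against.** Several stronger readings are tempting, and the article does not support them.

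- **That deaths are scored with their last CRS-R.** This is an inference. The carry-forward sentence concerns withdrawal, death is not among the four numbered reasons, and deaths have a separate survival analysis. What stands is that carry-forward is the only primary rule stated and death has no CRS-R rule. An analysis plan that is not shown could supply one, so this part asks the sponsor to define the scope of a stated rule.
- **That patients are credited with their last good value.** The text refers to the last evaluable assessment, which may already be lower. The score may predate the worsening, but need not.
- **That carry-forward and multiple imputation contradict each other.** Imputation can be read with the sensitivity analyses in the same sentence, or as meant for intermittent gaps. The roles are unclear, not incompatible.
- **That harm disappears from the trial.** Adverse events are recorded and tested (sections 2.3.6, 2.4 and 2.5). The effect is confined to the CRS-R comparison.
- **That the bias approaches a CRS-R point.** Dropout of 25% against 5% with 4 points of later recovery gives 0.20 × 4 = 0.8 points. That needs a 6-month primary endpoint and a dropout split that the article does not give, and the group comparison uses the index, not raw points.

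It is also fair to say that a mixed model or imputation under missing at random is no cure for withdrawal due to deterioration. Either may predict recovery for such a patient. This objection stands and shapes the fix.

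**Conclusion.** The point holds for withdrawn patients. The protocol itself fixes carry-forward for the primary analysis and exempts no withdrawal reason, including one closely tied to the outcome, so an analysis plan that is not shown does not remove the problem. The direction of the bias is unknown in advance. Its size is 0.05 to 0.20 SD under an assumed 10-point difference in dropout and 0.5 to 2 SD of common unobserved worsening, and zero if dropout and later change are the same across arms. It is small if only the post-session scores are primary and larger if the follow-up visits enter the ANOVA. For deaths and for multiple imputation, the supportable conclusion is lack of clarity, not error.

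**What to change.** Change section 2.2.3 as follows.

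1. Remove carry-forward from the primary analysis.
2. Name one primary method for all randomised patients: a mixed model for repeated measures, or multiple imputation using baseline and post-session scores. State the role of any other method.
3. Go on collecting CRS-R at the scheduled visits after withdrawal for deterioration, where consent allows.
4. State how death enters the CRS-R endpoint, for example as the worst rank in a composite analysed with a rank-based method, with a survivors-only sensitivity analysis. A worst rank does not fit directly into a mixed model, so the two must be planned together.
5. Add a delta-adjusted (missing not at random) sensitivity analysis for patients withdrawn for deterioration, because a missing-at-random method alone does not correct for it.

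The cost is new wording and some extra analysis work, with slightly wider intervals than carry-forward would give. The follow-up visits are already scheduled, though patients who revoke consent cannot be followed.
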